#### Additional covariates

Preoperative pain, attitude towards pain, and affective disorders (PPI, HADS, STAI, PCS, BRI, PSQ, DN4)Preoperative cognitive score (MoCA)EEG biomarkers from pre- and intraoperative EEG recordingsPreoperative blood biomarkersIntraoperative data related to anesthesia: anesthesia management, vital parameters, complicationsSurgical data: type of surgery, duration of surgery, complicationsClinical treatment data: demographics, medical history, sensory impairments (vision aids, hearing aids), medication history, preoperative substance abuse, intensive care unit stay, perioperative transfusions, complications, number and type of lines (e.g., intravenous lines, central venous catheters, arterial blood pressure monitoring, nasogastric or percutaneous feeding tube, suprapubic or urinary catheter, possibly other drains), discharge/transfer destination, length of stay

### Participant timeline {13}

Patients will receive one session of tES and will be visited postoperatively for 5 days (Table 1).

**Table 1 Tab1:** Schedule of intervention and visits

Timepoint	Measurement	Visits				
		V0	V1	V2	V3	V4–V13
*Time relative to surgery (D: day, H: hour)*		*D-1*	*H-1*	*H+0*	*H+1*	*D+1 to D+5 **twice daily*
**Enrollment**						
	Eligibility screening	x				
	Informed consent	x				
**Preoperative assessments**						
	Demographic data	x				
	Medical history	x				
	Baseline questionnaires	x				
	Cognitive status (MoCA)	x				
**Intervention**						
	Alpha-tACS/tDCS/sham				x	
**Postoperative assessments**						
	Arousal (RASS)		x		x	x
	POD (3D-CAM)		x		x	x
	Pain (NRS)		x		x	x
**Physical measures**						
	64-channel resting-state EEG recording (5 min)		x		x	
	Intraoperative frontal EEG recording			x		
	Blood draw		x		x	x (*only D+2* *morning*)

*Abbreviations*: *MoCA* Montreal Cognitive Assessment, *tACS* Transcranial alternating current stimulation, *tDCS* Transcranial direct current stimulation, *RASS* Richmond Agitation-Sedation Scale, *3D-CAM* 3-min diagnostic interview Confusion Assessment Method, *NRS* Numerical Rating Scale

### Sample size {14}

For the effect of tDCS on the frequency of postoperative delirium, the trial by Tao and colleagues observed a reduction from 19.7 to 4.9% [35] (odds ratio: 4.761). A previous study on the incidence of POD among general surgical patients at Greifswald University Hospital showed a prevalence of 22.2% [42]. We assume an effect similar to those of Tao et al. To demonstrate such an effect between the tACS group and the sham-stimulation group using a chi-square test with a power of 80% and a one-sided significance level alpha of 0.05, a group size of *N* = 60 is required. With 3 groups, and an expected dropout rate of about 20%, in total *N* = 225 participants should be included (Fig. 3).

**Fig. 3 Fig3:**
[figure not shown]
Flow-chart of the study processes. tACS transcranial alternating current stimulation, tDCS transcranial direct current stimulation

## Assignment of interventions: allocation

### Sequence generation {16a}

Assignment to the alpha-tACS, tDCS, and sham groups is done through stratified block randomization. Before the start of the study, a randomization sequence was created by a scientist who is not involved in the project. Using the R software (http://www.R-project.org), randomization blocks of different sizes were created. Participants will be then assigned to the tDCS, tACS, or sham group based on the generated randomization sequences within each block and stratum. The allocation to the experimental groups was done in a 1:1:1 ratio, with age (65–72 years and ≥ 73 years) and sex (men and women) serving as strata. Since the sham group was divided in n/2 tACS-sham and n/2 tDCS-sham, the intervention groups were also divided by two and a total of 6 groups were formed: 2x tACS, 2 × tDCS, 1 × sham-tACS, 1 × sham-tDCS. This repartition ensures that all groups are the same size, and that the frequency of an allocation will not allow tracing back to the intervention group.

### Concealment mechanism {16b}

A randomization sequence was created without allocation to a pseudonym or any specification for each stratum. Patients will be allocated to their group within the stratum following their order of enrolment.

## Assignment of interventions: blinding

### Who will be blinded {17a}

Everyone directly involved in this trial will be blinded to the interventions: patients, study staff, and care providers outside the study group. The analysis of the primary outcome will be undertaken before unblinding of the allocation sequence.

### Procedure for unblinding if needed {17b}

An Emergency Code Break was provided to the principal investigators, who can open it in emergency situations.

## Data collection and management

### Plans for assessment and collection of outcomes {18a}

#### Questionnaires

We will ask patients to report their pain level during rest and movement and the resulting disturbance on a Numerical Rating Scale from 0 to 10 (NRS) on the present day. We will furthermore ask patients to report the expected pain level in the PACU and 6 months after surgery during rest and movement. The Hospital Anxiety and Depression Scale (HADS) is a tool to detect states of depression and its severity [43]. The German adaptation has been validated [44]. The State-Trait Anxiety Inventory (STAI) score measures two types of anxiety: state anxiety, reflecting temporary feelings of anxiety, and trait anxiety, indicating a more general and long-term level of anxiety. The Pain Catastrophizing Scale (PCS) score measures the degree of catastrophizing thoughts and feelings individuals have about their pain. The Pain Sensitivity Questionnaire (PSQ) score quantifies an individual’s sensitivity to pain based on their responses to various hypothetical pain scenarios. The DN4 (Douleur Neuropathique en 4 Questions) questionnaire is a diagnostic tool used to identify neuropathic pain, consisting of 10 items that assess clinical symptoms and sensory signs.

#### Laboratory tests

Our study protocol mandates duplicate measurements for ELISA tests to bolster data quality. This practice aims to enhance precision, allow for the identification and correction of any technical errors, and ensure the reliability of our outcomes. We will use the LEGENDplex™ Human Neuroinflammation Panel 1 (13-plex) as well as single parameter ELISA for further specific biomarkers of interest.

### Plans to promote participant retention and complete follow-up {18b}

To improve the compliance, patients will be well-informed about the intervention and the postoperative visits. Patients are more likely to adhere to the trial protocol and complete all trial visits if they are thoroughly informed about the possible benefit and the very low risk associated with the intervention. Due to the short duration of the trial with a single tES application and the in-hospital context of the visits, we do not expect major issues with losses to follow-up.

If patients are discharged before the end of the postoperative observation period of 5 days, they will not be considered as loss to follow-up, as a stable neurocognitive outcome is considered as indispensable for patient discharge.

### Data management {19}

This trial was approved by the data protection officer of the Greifswald University Hospital. Clinical data will be collected in a pseudonymized form in a paper case report form (pCRF) for each patient. The digitalization into an electronic case report form (eCRF) will occur with a dual control principle to ensure minimization of transcription errors. Intraoperative EEG data will be collected anonymously; the assignment of the raw EEG traces to the patients will occur based on the date and time of the recording. The 64-channel EEG will be recorded with the ANT Neuro software using pseudonyms on a computer reserved solely for study purposes. Data will be kept for 10 years before being deleted or destroyed.

### Confidentiality {27}

Digital source data are stored on a study-specific, clinic-internal network drive with the corresponding pseudonym. Study leaders ensure through network permissions that only authorized study personnel have access. The allocation list of the pseudonyms will be kept in a locked cabinet.

The responsibility of transferring clinical study data to project partners rests with the aforementioned project leaders. If required, the collected study data may be shared with project partners within the scope of the GDPR, who can demonstrate a suitable data protection concept, for answering study-specific questions, in a pseudonymized form. The data will be published exclusively in an anonymized and aggregated form.

### Plans for collection, laboratory evaluation and storage of biological specimens for genetic or molecular analysis in this trial/future use {33}

The serum samples will be stored in the biobank of the Greifswald University Hospital until the end of the trial when all samples will be analyzed collectively. The aforementioned parameters will be determined. If recent scientific findings point towards new biomarkers of interest, the investigators leave themselves the option open to add those to the intended parameters.

## Statistical methods

### Statistical methods for primary and secondary outcomes {20a}

The statistical analysis will be based on the intention-to-treat principle, including all randomized patients in the groups to which they were assigned, regardless of the treatment received. The Statistical Analysis Plan will be publicly accessible on the clinical trial registry at https://drks.de/search/de/trial/DRKS00033703.

#### Primary outcome analysis

Binary logistic regression will be employed to adjust for baseline delirium status and to test differences between treatment (tACS) and control (sham) in incidence of POD. Dependent variable will be incidence of POD (yes/no); independent variables are group (tACS/sham) and baseline delirium status as measured by the 3D-CAM score. Odds ratio and corresponding 95% CI will be reported.

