#### Exclusion criteria

Known neurological or psychiatric conditions, especially history of epileptic seizuresContraindications for tDCS/tACS application [27]Long-term medication with central nervous system (CNS) active drugsIsolation due to multidrug-resistant germsInability of the patient to read and/or speak German

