### Intervention description {11a}

Patients will be enrolled at least 1 day before surgery. Questionnaires regarding contraindications for tES as well as baseline questionnaires will be handed out (PPI, HADS, STAI, PCS, BRI, PSQ, DN4). The preoperative cognitive status will be assessed with a MoCA score.

On the day of the surgery, a 64-channel EEG will be recorded in the preoperative holding area. Preoperative delirium and pain will be assessed with standardized tests (RASS, 3D-CAM, and NRS). A preoperative blood sample will be drawn. Before induction of anesthesia, a frontal EEG recording will be started that will last until the end of anesthesia.

A single tES intervention will take place postoperatively in the PACU, after return of consciousness and patient handover to the PACU staff. Emergence of delirium in the PACU (PACU-D) will be assessed, and patients will be asked about postoperative nausea and vomiting (PONV) as well as pain using standardized tests (RASS, 3D-CAM, and NRS) every 30 min for 1 h in the post-anesthesia care unit (PACU). A 64-channel EEG will be recorded, and a second blood sample will be drawn after the tES intervention.

During the first 5 postoperative days, patients will be screened twice daily for POD and pain using standardized tests (RASS, 3D-CAM, and NRS). A third blood sample will be drawn on the second postoperative day (Fig. 1).

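### The POD models adjust for a probably near-constant baseline 3D-CAM status and leave out the age and sex strata used in randomisation; the cost is small and so is the remedy

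*Protocol article*

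**What the plan says.** Protocol article, Primary outcome analysis: POD (yes/no) is analysed by binary logistic regression, and "independent variables are group (tACS/sham) and baseline delirium status as measured by the 3D-CAM score". An odds ratio with 95% CI is to be reported; the interval method is not named. Secondary outcome analysis repeats this model for tDCS against sham.

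Sequence generation {16a}: allocation is by stratified blocks, "with age (65–72 years and ≥ 73 years) and sex (men and women) serving as strata". Neither factor appears in the two POD models.

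Eligibility criteria {10}: surgery is elective, patients must be capable of consenting, and the exclusions include "Known neurological or psychiatric conditions" and long-term CNS-active medication. Delirium is not named as an exclusion. The baseline 3D-CAM is taken on the day of surgery, after enrolment (Intervention description {11a}): "Preoperative delirium and pain will be assessed with standardized tests (RASS, 3D-CAM, and NRS"). MoCA is collected before surgery and listed under Additional covariates {12}, outside the primary model.

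Sample size {14}: the planning source "observed a reduction from 19.7 to 4.9" per cent. The calculation uses a chi-square test with "a power of 80% and a one-sided significance level alpha of 0.05", giving 60 per group and 225 in total after 20% dropout.

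**The concern.** A baseline covariate earns its place in a primary model by varying between patients and predicting the outcome. Preoperative delirium predicts POD almost by definition, but in this population it will hardly vary. In many trials of this size it would be constant or carried by one to three patients, so the adjustment the protocol promises would do little or nothing.

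The factors that do vary, and that the trial judged important enough to stratify on, are left out. If age and sex predict POD, stratifying on them and then ignoring them normally yields standard errors that are slightly too large, and it discards some prognostic information.

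The third strand is sparse data. The planning rates imply few POD cases, particularly under tACS. With no case in that arm, ordinary maximum likelihood gives no finite odds ratio, just when the treatment looks most effective.

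**Working it through.** **Plan's own figure.** Control rate 0.197, active rate 0.049, mean 0.123, one-sided 0.05, power 80%, pooled variance, no continuity correction:

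n = [1.645·√(2·0.123·0.877) + 0.842·√(0.197·0.803 + 0.049·0.951)]² / 0.148² = 59.8, so 60 per group. Then 60/0.8 = 75 and 3 × 75 = 225. The odds ratio is (0.197/0.803)/(0.049/0.951) = 4.76. All stated figures reproduce and none depends on this point.

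**How often the covariate is constant.** The protocol gives no prevalence π of a positive baseline 3D-CAM, so π is assumed. P(no positive among N) = (1 − π)^N.

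| Assumed π | N = 120 | N = 150 |
|---|---|---|
| 0.5% | 55% | 47% |
| 1% | 30% | 22% |
| 2% | 9% | 5% |

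Expected positives among 120 patients are 0.6, 1.2 and 2.4. If 90% of them are also POD-positive (assumed), the baseline coefficient itself is non-finite in a further 43%, 63% and 72% of trials at 60 per arm.

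**Does that damage the treatment estimate?** Same assumptions, 60 per arm, share of trials with a non-finite treatment odds ratio:

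| Assumed π | With baseline 3D-CAM | Without |
|---|---|---|
| 0.5% | 4.9% | 3.7% |
| 1% | 4.9% | 2.9% |
| 2% | 4.4% | 1.7% |

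The covariate adds about 1 to 3 points. The main source is an empty tACS event cell: 0.951^60 = 4.9%, or 0.951^75 = 2.3%. Expected events in the comparison are 60 × (0.197 + 0.049) = 14.8, or 75 × 0.246 = 18.5.

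**Power cost of keeping baseline 3D-CAM** (3,000 simulated trials, 60 per arm, one-sided 0.05 Wald test, adjusted against unadjusted): 76.8% v 77.1% at π = 0.5%, 76.1% v 76.8% at 1%, 76.0% v 74.9% at 2%. There is no material loss.

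**Power from adding the strata and MoCA** (12,000 simulated trials, 60 per arm, one-sided 0.05 Wald test, marginal rates held at 19.7% and 4.9%, all prognostic odds ratios assumed):

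| Assumed ORs: age, sex, MoCA per SD | Group only | + age, sex | + MoCA |
|---|---|---|---|
| 1, 1, 1 | 76.9% | 77.3% | 76.8% |
| 2, 1.3, 1.5 | 77.2% | 77.9% | 78.0% |
| 3, 1.5, 2.5 | 77.5% | 78.2% | 80.5% |

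The Monte Carlo error of each entry is about √(0.77·0.23/12,000) = 0.4 point. At 75 per arm the total gain is about 1 point, rising to 2 to 3 points with strong predictors.

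**Choice of test** (exact enumeration of unadjusted 2×2 tables at the planning rates, 60 per arm):

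| Method | Two-sided 5% | One-sided 5% |
|---|---|---|
| Wald | 62.9% | 76.7% |
| Likelihood ratio | 75.4% | 82.6% |
| Pearson | 72.5% | 82.6% |
| Firth penalised likelihood | 71.0% | 82.5% |

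Two-sided type I error at event rates of 10% to 20% is 5.4% to 6.1% for the ordinary likelihood ratio and 4.2% to 4.6% for Firth. At 75 per arm, two-sided, Wald has 76.9% and Firth 81.8%.

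**Empty cell under Firth.** For 0/60 against 12/60, the penalised odds ratio is (0.5 × 48.5)/(60.5 × 12.5) = 0.032. It is finite, and so is its profile interval.

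**The case against.** A reader might infer three stronger things, and the documents support none of them.

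*The primary model may fail to give an estimate because of its covariate.* A constant covariate is aliased and dropped. A separated one leaves only its own coefficient infinite. The treatment odds ratio stays finite in about 95% of trials or more, and the failures come mainly from zero tACS events, which a change of covariates does not cure. All randomised patients are to be analysed and missing data imputed, so 75 per arm and 2.3% may be nearer the mark than 60 and 4.9%.

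*The model gives away substantial power.* The covariate part is 0 to 3 points, and the top of that range needs a very strong assumed MoCA effect. The larger gap, from 63% to 71%, compares a two-sided Wald test with a Firth test. The protocol names no Wald interval and plans its sample size one-sided. An ordinary likelihood-ratio test already reaches 75.4%, with a slightly raised type I error.

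*Omitting the strata makes the analysis invalid.* Omission after stratified randomisation is normally conservative, and nothing here shows an inflated type I error.

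Two further points stand. Near-constancy is an inference from eligibility, since delirium is not a named exclusion and the 3D-CAM follows enrolment. The interval method and a sparse-data fallback are also matters a protocol may leave to its analysis plan, so their absence here is not a fault. MoCA is already foreseen in exploratory subgroup models by baseline cognitive function, and its place in the primary model is a matter of preference.

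What the objection does not remove is that the covariate set is stated outright, and that it differs from the trial's own stratification.

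**Conclusion.** The point holds as a modest mismatch between design and analysis. Both POD models carry one covariate that is probably close to constant and omit the two factors that stratify the randomisation. The expected gain from correcting this is about 0.5 to 1 point of power for the strata and 0 to 3 points if MoCA is added. The present test is at worst slightly conservative, and the treatment odds ratio is usually estimable. Zero tACS events, with a 2% to 5% chance at the planning rates, is a separate sparse-data matter best met by the choice of likelihood.

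The prevalence of baseline delirium, the share of those patients who go on to POD, and all prognostic odds ratios are assumptions. The event rates and group sizes are the protocol's own. The change is worth making because it costs almost nothing, not because the primary result is in danger.

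**What to change.** In the primary (tACS) and secondary (tDCS) POD models, replace baseline 3D-CAM status with age stratum (65–72, 73 and over) and sex. Add a sensitivity analysis that excludes patients who were 3D-CAM positive before surgery, since their later positive screens are doubtful as new cases. State that the test and 95% CI come from the likelihood, preferably Firth-penalised with a profile interval, rather than from Wald, so that a usable interval exists even with no tACS events. MoCA may be added but is not needed.

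Cost: wording in the protocol and analysis plan, settled before unblinding; every variable is already collected. Each model has one more term than planned (group, age, sex instead of group, baseline 3D-CAM) on about 15 to 18 events. The reported odds ratio becomes conditional on age and sex, which the report should say.

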#### Secondary outcome analysis

Binary logistic regression will be employed to adjust for baseline delirium status and to test differences between treatment (tDCS) and control (sham) in incidence of POD. Dependent variable will be incidence of POD (yes/no); independent variables are group (tDCS/sham) and baseline delirium status as measured by the 3D-CAM score. Odds ratio and corresponding 95% CI will be reported.Continuous variables (e.g., duration of delirium, severity scores, EEG biomarkers, fluid biomarkers) will be analyzed using analysis of covariance (ANCOVA) including the particular baseline value.Categorical variables (e.g., delirium phenotype) will be analyzed using binary logistic regression, adjusting for baseline 3D-CAM.For EEG and biofluid biomarker outcomes, linear mixed-models (LMM) will be implemented to account for within-subject correlations across time points.

In addition to the primary and secondary outcomes, exploratory analyses will be conducted on the collected blood samples to gain further insights into the biological mechanisms associated with postoperative delirium (POD) and the effects of transcranial electrical stimulation (tES). These analyses will focus on identifying associations between levels of various blood biomarkers—particularly markers of neuroinflammation, neurodegeneration, and other relevant pathways—and the incidence and severity of POD. Additionally, we aim to explore potential biomarkers that may be associated with differential responses to the tES intervention.

To better understand how patient characteristics influence treatment response, we will conduct subgroup analyses using blood biomarker profiles. These profiles, identified through exploratory cluster analysis, will help us group patients into distinct subgroups with potentially unique responses to tES. This approach could uncover specific biomarker patterns linked to differential treatment effects, paving the way for personalized POD prevention strategies. Recognizing the heterogeneity of our study population is crucial for interpreting our findings and guiding future research towards biomarker-driven, individualized treatments [45]. Our discussion will highlight the importance of considering patient diversity in POD risk and treatment response.

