## Objectives {7}

The objective of this study is to investigate the effects of tES on the incidence of POD and postoperative pain. As primary objective, the effect of tACS in the alpha frequency range (alpha-tACS) on the incidence of POD after major surgery will be examined in comparison to sham stimulation. In a second study arm, the effect of tDCS compared to sham stimulation on the incidence of POD will be investigated. The effect of tES on postoperative pain will be investigated as a secondary outcome, for both intervention groups in comparison to sham stimulation. To identify potential predictors of the responsiveness to tES and to address the multifactorial genesis of POD and postoperative pain, we plan to assess neuronal network dysfunction with pre-, intra-, and postoperative EEG recordings but also neurotransmitter disbalance and neuroinflammation/-destruction using biofluid blood biomarkers. Furthermore, the influence of intraoperative medication, type and length of surgery, and vital parameters on the endpoints will be considered. Potential predictors of response to tES will thus be identified.

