### Methods for additional analyses (e.g., subgroup analyses) {20b}

Subgroup analyses will be conducted to explore the differential effects of alpha-tACS and tDCS in specific patient subsets, such as by age, sex, type of surgery, or baseline cognitive function.

All subgroup analyses will be exploratory. According to the European Medicines Agency (EMA) Guideline on subgroup analyses in confirmatory trials (2019, January 31) and the NEJM publication on reporting of subgroup analyses the regression models with interaction terms of subgroups by treatment form the starting point of the subgroup analyses with separate models for each of the subgroup analyses [46]. Additionally, we will provide subgroup specific estimates with 95% CI based on these models using a forest plot to allow exploratory evaluation on the direction and magnitude of treatment effects in subgroups. Estimates derived from exploratory subgroup analyses should be interpreted with caution.

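### The stated models for continuous secondary outcomes do not carry in type and duration of surgery, although the protocol lists both as covariates; adding them is valid and may gain some precision for pain and blood markers

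*Protocol article*

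**What the plan says.** Under *Secondary outcome analysis*, the outcomes introduced by "Continuous variables (e.g., duration of delirium, severity scores, EEG biomarkers, fluid biomarkers" and a closing bracket "will be analyzed using analysis of covariance (ANCOVA) including the particular baseline value". No other covariate is named. For EEG and blood markers the same section adds that "linear mixed-models (LMM) will be implemented to account for within-subject correlations across time points", again without naming covariates. Pain on the NRS is a secondary outcome but is not among the examples; it comes under the ANCOVA sentence only through the open-ended list.

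Elsewhere the article treats surgery as relevant. *Objectives {7}* states that "the influence of intraoperative medication, type and length of surgery, and vital parameters on the endpoints will be considered". *Additional covariates* includes "type of surgery, duration of surgery" among the data to be collected. The section on additional analyses plans exploratory subgroup models with interaction terms, "such as by age, sex, type of surgery, or baseline cognitive function".

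On design, *Intervention description {11a}* says that "A single tES intervention will take place postoperatively in the PACU". *Sequence generation {16a}* describes randomisation "with age (65–72 years and ≥ 73 years) and sex (men and women) serving as strata"; surgery is not a stratum.

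**The concern.** The trial pools general, urological, gynecological, orthopedic and spinal operations of any length above 60 minutes. The protocol itself names type and length of surgery as possible influences on the endpoints. If they do influence postoperative pain and inflammatory markers, the variance between operations stays in the error term of a model that contains only the outcome's own preoperative value. The only stated modelling use of surgery type is the exploratory interaction analysis, which asks whether the effect differs between fields and does not sharpen the overall comparison.

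At stake is the precision of the pain and blood-marker comparisons. Pain is part of the trial's stated objective, and the blood markers are meant to show what stimulation does. There is a second, smaller point. *Additional covariates* is a long list, and not fixing which of its entries enter the models leaves room for a choice after unblinding.

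**Working it through.** **1. The plan's own figure.** *Sample size {14}* gives 60 per group from 19.7% versus 4.9%, 80% power and one-sided alpha 0.05. With the usual formula without continuity correction and a mean proportion of 0.123:

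n = [1.645·√(2·0.123·0.877) + 0.842·√(0.197·0.803 + 0.049·0.951)]² / 0.148² = 59.8, so 60.

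Three groups make 180, and 180/0.80 = 225. Both figures reproduce. They concern the binary primary outcome; the article gives no SD, power or precision target for any secondary outcome. Only the 60 analysed per arm is carried forward.

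**2. Is adjustment valid?** Type and duration of surgery are complete before stimulation starts in the recovery room. *Who will be blinded {17a}* lists patients, study staff and care providers outside the study group. Neither variable can be changed by the stimulation, and both are already collected.

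**3. Reference precision.** Take the SD left after own-baseline adjustment as 1. With 60 per arm, the SE of the difference is √(2/60) = 0.183. The difference detectable with 80% power at two-sided 5% is (1.960 + 0.842)·0.183 = 0.51 SD.

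**4. Effect of adding surgery.** Let R² be the share of that remaining variance explained by type and duration. The documents give no value, so a range is shown. Five extra parameters are assumed: four indicators for five fields, plus duration. Their approximate cost, with 120 patients and eight coefficients, is √(1 + 5/(120 − 8 − 1)) = 1.022. Then:

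SE ratio = √(1 − R²) · 1.022

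Equivalent change in patients = 1/(SE ratio)² − 1

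Power for a true difference of 0.5 SD = Φ(0.5/(0.183 · SE ratio) − 1.96)

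| Assumed R² | SE ratio ignoring parameter cost | SE ratio with five parameters | Equivalent change in patients | Power at 0.5 SD |
|---|---|---|---|---|
| Baseline-only model | – | 1 | – | 78% |
| 0 | 1.000 | 1.022 | −4% | 76% |
| 0.02 | 0.990 | 1.012 | −2% | 77% |
| 0.05 | 0.975 | 0.996 | +1% | 78% |
| 0.10 | 0.949 | 0.970 | +6% | 81% |
| 0.20 | 0.894 | 0.914 | +20% | 85% |
| 0.30 | 0.837 | 0.855 | +37% | 89% |

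Break-even is where (1 − R²)(1 + 5/111) = 1, that is R² = 5/116 = 0.043.

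**5. Adding the strata.** Age group and sex as two further parameters raise the cost factor to √(1 + 7/109) = 1.032, about one percentage point more, before any variance that they explain.

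**6. Chance imbalance.** For a surgical field that makes up 30% of patients (an assumed share), the between-arm difference in share has SD √(2·0.3·0.7/60) = 8 percentage points. This is ordinary sampling variation, which the SE already reflects; adjustment removes part of it.

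**The case against.** The strongest reply is that the article refers to a separate statistical analysis plan, not shown here, which may name the covariates. ANCOVA on the outcome's own baseline is a standard and valid analysis, and the sentence says that the baseline is included, not that nothing else is. That stands in part: a reader might infer that the plan disregards surgery altogether, and the documents do not support this, since two sections provide for it. What remains is that the article declares these covariates, then sets out its models, and the two are not connected.

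A reader might also infer that the unadjusted comparisons are biased. They are not: under randomisation, an imbalance in surgical mix is chance and is covered by the SE.

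Nor may a definite loss of precision be inferred. No R² is given, and surgical specialty is a coarse grouping, so 0.20 to 0.30 is not assured. Calculations that charge nothing for the extra parameters look too favourable: they give a 5% smaller SE at R² 0.10, against 3% here. That pain and inflammatory markers vary with the operation is a clinical expectation rather than a figure in the documents. The protocol shares it only as far as naming surgery as a possible influence.

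Two limits of scope also stand. Pain is covered by the ANCOVA sentence only by implication. For postoperative resting EEG, nothing in the documents suggests that surgery type adds much beyond the EEG's own baseline.

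**Conclusion.** The point holds as an efficiency improvement in secondary outcomes. The treatment-comparison models do not take up the stated intention to consider type and duration of surgery, although adjusting for both is valid, needs no new data and is not made redundant by the stratification.

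With 60 analysed per arm and about five extra parameters, the SE is roughly unchanged at R² 0.05 and falls by 3%, 9% and 14% at 0.10, 0.20 and 0.30. The worst case is an SE 1 to 2% larger if surgery explains little or nothing. All of this rests on assumed R² values and an approximate parameter cost. The sample size and the stated primary analysis are not affected. The change is worth making because its possible gain exceeds its possible loss and it settles the covariates in advance.

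**What to change.** Before unblinding, specify in *Secondary outcome analysis*, and identically in the statistical analysis plan, that the models for NRS pain and blood markers include:

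- the outcome's own baseline value;
- type of surgery, using the specialties in the inclusion criteria, with a pre-stated rule for merging small ones;
- duration of surgery;
- the randomisation strata, age group and sex, which these models do not name either.

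Name pain explicitly as an outcome analysed this way. Keep the baseline-only model as a sensitivity analysis. Adding surgery to the EEG models is optional. Enter nothing measured after stimulation as a covariate. If the unseen analysis plan already contains such a list, aligning the article's wording with it is enough.

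The cost is a sentence or two and about seven parameters out of at least 120 patients per comparison, with no new data or visits.
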